### Data collection and follow-up

Data will be collected on paper-based forms and in a secure electronic database for further analysis.

#### Clinical data

Personal data (age, sex, height); CV risk factors (smoking, alcohol use, weight, body mass index); comorbidities (diabetes, hypertension, coronary artery disease, heart failure etc); physical examination (blood pressure, heart rate, crackles, pedal edema etc); type of renal disease; renal function (urea, creatinine, proteinuria, etc); medication; inflammation evaluation: CRP; complete blood count will be collected.

For the dialysis population: dialysis vintage and for the transplantation population: dialysis vintage before transplantation; date of transplantation, type (living or cadaveric donor), mismatch number, type of induction therapy; type of chronic immunosuppression therapy, will be also collected. Supplementary, for the COVID arm, we will assess also the severity of the infection, administered treatment, use of oxygen therapy, vaccination status.

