**Trial registration:**

Patient enrolment in the trial started in January 2021 and is expected to finish at the end of 2022. The study can be found on ClinicalTrials.gov database with NCT05125913 identifier.

Registered on 18 November 2021 - Retrospectively registered.

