### Study population

We aim to enrol 250 patients, divided into two groups with minimum 125 patients per group: COVID group and non-COVID group. Both groups will be monitored at 6, 12 and 24 months since the first procedure visit, defined as the baseline.

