#### Inclusion criteria

Age > 18 years;Patients with CKD stage 3–5, including dialysis or KTx with confirmed COVID-19, at minimum 2 weeks after the confirmed test;Age, sex and kidney disease (CKD stage 3–5, dialysis or KTx) matched patients without confirmed SARS-CoV-2 infection.

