### Statistical analysis

The statistical analyses will be performed using the SPSS for Windows, version 19.0.1, R (version 3.1.2) package for statistical analysis and STATA 13. Non-normally distributed variables will be expressed as median with interquartile range and normally distributed variables as mean ± SD, as appropriate. Between-group comparisons will be assessed for nominal variables with the Chi-square test, and by Kruskal-Wallis test or one-way ANOVA for the rest of the variables. In order to comply with the assumptions for regression analysis, logarithmic conversion will be performed for non-normally distributed variables. Pearson correlation coefficient will be used to determine correlations between variables. Stepwise multivariate regression analysis including all univariate associates (*p* < 0.05) will be used to assess the independent associations between variables. Survival and time-to-event analysis of outcomes will be performed using Kaplan-Meier cumulative survival plots and Cox proportional hazards model, including adjustment for potential confounding factors. In the multivariate Cox models, we will adjust for all variables that will be correlated to the study outcomes with *P* < 0.05 at univariate Cox analyses.

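### Vaccination status is to be recorded only in the COVID arm, so the between-arm comparison can neither describe nor adjust for it

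*Protocol article*

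**What the plan says.** The Clinical data section has three tiers. The first applies to all patients and runs from demographics and comorbidities to "medication; inflammation evaluation: CRP; complete blood count will be collected". The second adds items for dialysis and transplant patients. The third reads: "for the COVID arm, we will assess also the severity of the infection, administered treatment, use of oxygen therapy, vaccination status". The article names vaccination status nowhere else as a collected item, an eligibility criterion, a matching factor or a covariate.

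The Inclusion criteria define the controls as "Age, sex and kidney disease (CKD stage 3–5, dialysis or KTx) matched patients without confirmed SARS-CoV-2 infection". The Statistical analysis section plans Cox models "including adjustment for potential confounding factors", and for the multivariate models states that "we will adjust for all variables that will be correlated to the study outcomes" at P < 0.05 in univariate Cox analysis. On timing, the Trial registration paragraph says "Patient enrolment in the trial started in January 2021 and is expected to finish at the end of 2022", and the Study population section says "Both groups will be monitored at 6, 12 and 24 months since the first procedure visit".

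**The concern.** The comparison is not randomised. Arm membership depends on confirmed infection, and the main outcomes include all-cause mortality and a composite cardiovascular outcome. A factor that changes the chance of infection and also the chance of a later event is a confounder of that comparison. Vaccination is a plausible one, and enrolment over 2021 and 2022 allows vaccination status to differ between patients and over time.

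Severity, treatment and oxygen use have no counterpart in controls, so collecting them in one arm is sensible. Vaccination status does have a counterpart. If it is collected in one arm only, a reader of the results cannot see whether the arms differed on it, and the analyst cannot take any difference out of the estimated COVID-19 effect.

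**Working it through.** **1. The plan's own figure.** The sample size section gives 9% v 22% mortality, alpha 0.05 and 125 per group for 80% power. Two-sided alpha is assumed, because the article does not state sidedness, and no continuity correction is used.

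- Mean proportion = (0.09 + 0.22)/2 = 0.155.
- n = [1.960 × √(2 × 0.155 × 0.845) + 0.842 × √(0.09 × 0.91 + 0.22 × 0.78)]² / 0.13² = 121 per group.
- Power with 125 per group = 81.4%.

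The stated power is reproduced, and nothing in this point changes it. The planned mortality ratio is 0.22/0.09 = 2.44.

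**2. Can the planned model use the variable?** With vaccination recorded only in the COVID arm:

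- A complete-case two-arm Cox model that includes it drops every control.
- Imputation for controls has no observed control value to learn from.
- The univariate screen can assess it only within the COVID arm.
- Matching on age, sex and kidney disease category does not balance it.

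The missingness of the variable coincides exactly with arm. Vaccination itself need not.

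**3. How large could the bias be?** The documents give no coverage and no vaccine effect, so every input here is an assumption. Let v1 and v0 be the vaccinated fractions in the COVID and control arms, and let rr be the mortality ratio of vaccinated to unvaccinated patients. With no true COVID-19 effect, the spurious ratio is

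(1 − v1(1 − rr)) / (1 − v0(1 − rr)).

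| v1 (COVID) | v0 (control) | rr = 0.9 | rr = 0.5 |
|---|---|---|---|
| 50% | 60% | 0.95/0.94 = 1.01 | 0.75/0.70 = 1.07 |
| 20% | 40% | 0.98/0.96 = 1.02 | 0.90/0.80 = 1.13 |
| 30% | 60% | 0.97/0.94 = 1.03 | 0.85/0.70 = 1.21 |
| 20% | 70% | 0.98/0.93 = 1.05 | 0.90/0.65 = 1.38 |

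- Extreme inputs: 30% v 80% with rr = 0.3 gives 0.79/0.44 = 1.80.
- Reversed coverage: 60% v 30% with rr = 0.5 gives 0.70/0.85 = 0.82, which would hide a harm.

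**4. Effect on a test.** Take control mortality at 9%, 125 per group, and the largest ratio in the table. COVID-arm mortality becomes 0.09 × 1.385 = 12.5%. The chance of a significant result in the direction of harm is then about 14%, against a nominal 2.5% in that direction. For the 30% v 60%, rr = 0.5 case it is about 7%, and for 50% v 60%, rr = 0.5 about 4%.

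**5. Which vaccinations count.** COVID patients may enter from two weeks after the confirmed test, and the Inclusion criteria set no upper limit on that interval. Doses given between infection and the baseline visit are therefore possible. Such doses follow the exposure and may be influenced by it, so status at baseline is not the same as status before infection. Controls have no infection date, and the article defines no reference date for them.

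**The case against.** Several objections have force.

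- **The gap is recoverable.** Screening and enrolment provides a detailed baseline interview and use of the electronic medical record, and both groups return at 6, 12 and 24 months. A reader might infer that the comparison is beyond repair. That would be true only if the data were never obtained. This stands.
- **The importance of the confounder is not shown.** The article gives no coverage by arm, no vaccine effect and no direction of imbalance. Many deaths in this population may have nothing to do with infection, which would pull rr towards 1. The illustration also holds coverage fixed for 24 months, and later uptake could narrow a gap. A reader might infer that vaccination is a major confounder that always exaggerates harm. The documents support neither part of that. This stands.
- **The variable can still be used within the COVID arm.** Listed beside severity and treatment, it may have been meant to describe the infection episode. That purpose is coherent, but it does not serve the between-arm comparison.
- **This is a condensed article, and the case report form is not shown.** Control status might be recorded in practice, or the general medication item might be read to include vaccines. This lowers certainty a little. However, the article is not silent: it names the item separately and assigns it to one arm, which argues against the wider reading. An analysis plan could not adjust for data that were not collected.

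**Conclusion.** The point holds in limited form. Followed as written, the plan leaves vaccination status unknown for all controls, so its promised confounder adjustment cannot include a plausible common cause of infection and outcome. Any imbalance could be neither described nor removed.

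The size rests wholly on assumptions. It runs from negligible (about 1.0) to moderate (about 1.4), reaches 1.8 only with extreme inputs, and falls below 1 if coverage is reversed. None of these reaches the planned ratio of 2.44, so a reader should not infer that vaccination alone would produce the planned contrast. A true effect smaller than planned could still be materially distorted.

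It would also go too far to say that vaccination is perfectly confounded with arm, because only its missingness is. The gap is inexpensive to close through interview, records and scheduled visits.

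**What to change.** 1. Move vaccination status, as number of doses and dates, from the COVID-arm supplement to the baseline data common to both arms.
2. For controls already enrolled, retrieve it by interview or from medical records.
3. Record later doses in both arms at the 6, 12 and 24 month visits.
4. Define a reference date for each control that corresponds to the infection date of the matched COVID patient.
5. Pre-specify vaccination before infection, or before that reference date, as an adjustment covariate in the between-arm models regardless of its univariate P value. The plan's own rates imply only about 0.09 × 125 + 0.22 × 125 = 38.75 deaths, so a P < 0.05 screen could easily miss a real confounder.
6. Report later vaccination descriptively only. It is post-exposure, and adjusting for it, including as a time-dependent covariate, can itself introduce bias.

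The cost is one extra form item and a record look-up for controls already enrolled. Sample size and visit schedule are unchanged.

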### Outcome data

***The primary outcomes of this study*** will be all-cause mortality rate, a composite CV outcome (time to first non-fatal myocardial infarction, non-fatal stroke, and hospitalization for heart failure or CV death) and long-term impact of the COVID-19 on markers of CV risk and ED in all included patients.

***Secondary outcomes*** are defined as a composite of renal outcome: doubling of creatinine or a 40% decline in eGFR or dialysis initiation in CKD or KTx patients.

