### Objectives

The objectives of this observational study are to determine:the feasibility of flow mediated dilation (FMD), bioimpedance spectroscopy (BIS) fluid assessment, lung ultrasound (LUS) and pulse wave velocity (PWV) measurement in CKD patients following COVID-19 and matched CKD control-patients without a history of previous SARS-CoV-2 infection;the long-term impact of the COVID-19 on markers of CV risk and ED in patients with CKD and KTx on a composite CV outcome (time to first non-fatal myocardial infarction, non-fatal stroke, hospitalization for heart failure or CV death) and on all-cause mortality;the long-term impact of the COVID-19 on markers of CV risk and ED in patients with CKD and KTx on a composite renal outcome: doubling of creatinine or a 40% decline in eGFR or dialysis initiation.

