### Sample size power calculation

According to sample size power calculations, including 125 patients in each group will provide statistical power (alpha 0.05 and power 80%) for an estimated difference in the mortality rate of 9% [29] in the non-COVID group compared to 22% mortality in the COVID positive group [30–34].

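### The renal composite counts starting dialysis but not kidney transplantation, so kidney failure treated first by a transplant can go uncounted

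*Protocol article*

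**What the plan says.** The renal composite is defined twice in the protocol article. The Objectives give a "composite renal outcome: doubling of creatinine or a 40% decline in eGFR or dialysis initiation". The Outcome data section makes it the secondary outcome and names the patients it applies to: "doubling of creatinine or a 40% decline in eGFR or dialysis initiation in CKD or KTx patients". Both lists have the same three components. Neither mentions transplantation, re-transplantation, graft failure or kidney replacement therapy in general.

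The cohort includes patients who could be transplanted without prior dialysis. The Inclusion criteria admit "Patients with CKD stage 3–5, including dialysis or KTx with confirmed COVID-19, at minimum 2 weeks after the confirmed test", together with matched patients without confirmed infection. Follow-up is long enough for it to happen: "Both groups will be monitored at 6, 12 and 24 months since the first procedure visit, defined as the baseline". Table 1 assesses the renal outcome at 6, 12 and 24 months.

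Transplant details are collected under Clinical data, including "dialysis vintage before transplantation; date of transplantation, type (living or cadaveric donor", but for the transplanted population and with no link to the renal outcome. The Statistical analysis section says "Survival and time-to-event analysis of outcomes will be performed using Kaplan-Meier cumulative survival plots and Cox proportional hazards model". It does not say how a transplant during follow-up is handled.

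**The concern.** Dialysis and transplantation are two treatments for the same state, kidney failure. A composite that counts one and not the other makes the event depend on which treatment came first. Once a new kidney is in place, creatinine falls and eGFR rises, so the two laboratory components can no longer pick up the failure of the native kidneys or of the earlier graft.

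This composite is the only secondary outcome and the subject of one of the three objectives. At stake is a loss of genuine kidney-failure events. If transplant access were to differ between the COVID and non-COVID groups, the loss would be unequal between the groups being compared.

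**Working it through.** **1. The plan's own figure.** The only computed design figure concerns mortality, not the renal outcome: "including 125 patients in each group will provide statistical power (alpha 0.05 and power 80"%), for 9% "in the non-COVID group compared to 22% mortality in the COVID positive group". With a two-sided alpha of 0.05 and the usual two-proportion formula:

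- pooled proportion = (0.09 + 0.22)/2 = 0.155
- SE under no difference = √(2 × 0.155 × 0.845/125) = 0.0458
- SE under the alternative = √((0.09 × 0.91 + 0.22 × 0.78)/125) = 0.0450
- z = (0.13 − 1.96 × 0.0458)/0.0450 = 0.89, so power is 81.4%

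The stated 80% reproduces. Nothing in this point changes it, and no power calculation rests on the renal composite.

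**2. Which patients fall through.** Under the 40% rule a patient counts at 0.6 × baseline eGFR or below. The baselines here are illustrative:

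| Baseline eGFR | Counts at or below |
|---|---|
| 15 | 0.6 × 15 = 9.0 |
| 12 | 0.6 × 12 = 7.2 |
| 10 | 0.6 × 10 = 6.0 |

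A stage 5 patient transplanted above this level, without doubled creatinine and without dialysis, meets no component. A second route is timing. Where a qualifying fall and the transplant both occur between scheduled visits, for example between months 12 and 24, the fall may never be recorded.

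Two kinds of patient are not affected. One who met the creatinine or eGFR criterion on record before the transplant already counts. One already on dialysis at baseline cannot start it.

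**3. Size.** The document gives no renal event rate, no transplant rate and no split of the cohort by type of kidney disease. All three inputs below are assumptions:

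- patients at risk: 150 of the planned 250
- risk of a counted event: 20%, so 150 × 0.20 = 30 counted events
- transplantation before dialysis: 1%, 2% or 4%

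Uncounted share = m/(30 + m), where m is the number of such transplants:

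| Transplant rate | m | Share of all renal events |
|---|---|---|
| 0% | 0 | 0% |
| 1% | 1.5 | 1.5/31.5 = 4.8% |
| 2% | 3 | 3/33 = 9.1% |
| 4% | 6 | 6/36 = 16.7% |

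Given these inputs the shares are upper bounds, because the formula supposes that none of the m patients had already met another component. The 150 cancels: the share equals rate/(risk + rate), so it depends only on the two assumed percentages, and a lower event risk would raise it. The top of the range is demanding. If only 30 of the 150 were near kidney failure (again illustrative), 6 transplants would be 6/30 = 20% of them.

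**The case against.** The strongest reply is that the consequence is narrower than it looks. A reader might infer that every patient transplanted before dialysis is scored event-free. The definition does not support that: a patient whose creatinine had doubled or whose eGFR had fallen by 40% on record beforehand is already an event. Patients with a failing graft may often be in that position. This stands, and the point is limited accordingly.

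A reader might also infer that such a patient is then followed as a renal success. The article does not say so. Censoring at transplant, or treating it as a competing event, is equally compatible with its text, and such rules may properly sit in an analysis plan that is not shown. Their absence is therefore no finding. But neither rule would make the transplant an event. The list of components is fixed in this document, and an analysis plan could not extend it without changing the endpoint.

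Finally, the size rests wholly on assumed inputs. Recruitment is partly from dialysis units, so fewer than 150 patients may be at risk, and a difference in transplant access by COVID status has no support in the document. All of this stands. It limits the size of the problem, not its existence.

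**Conclusion.** The point holds in a limited form. The composite, as defined in both places, does not count a transplant or re-transplant during follow-up in a patient who was not on dialysis at baseline and had no earlier recorded component. The same failure treated by dialysis counts. No other section closes the gap.

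The number affected is unknown, probably small, and nil if no such transplant occurs. The range of about 5–17% of renal events is an upper bound resting on three assumed inputs, not an estimate from the document.

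It would go too far to conclude that the comparison between COVID and non-COVID groups is biased. That requires COVID status to change access to transplantation, which the document neither states nor implies. Without it, the consequence is a few lost events in a secondary outcome. The correction is still worth making, because the definition treats one clinical state in two ways and the change is cheap.

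**What to change.** In the Objectives and in Outcome data, for patients not on dialysis at baseline, define the last component as: *initiation of dialysis or kidney transplantation (first or repeat) during follow-up, whichever is earlier*. Add that creatinine and eGFR values obtained after a transplant that takes place during follow-up are not used for the other two components.

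Two limits in this wording matter:

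- **During follow-up.** Every value in a patient enrolled with a graft is obtained after a transplant. Without the limit, the rule would remove both laboratory components for the whole transplanted group. Values from a graft in place at baseline stay in use.
- **Not on dialysis at baseline.** The Inclusion criteria can be read as including dialysis patients within CKD stage 3–5. Without the limit, transplantation of a patient already on dialysis could be scored as an adverse renal event.

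The cost is one line in each definition and one dated item on the follow-up form, since transplants during follow-up must now be recorded. Clinical data are already scheduled at every visit and hospitalizations are tracked through the electronic record, so the added work is small. The change concerns outcome classification only and leaves patient care and the mortality sample size untouched.

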### Strategies to ensure adequate enrolment and protocol compliance

Report forms will be uploaded into a secure database in a timely manner. This will allow periodical checks for enrolment rates, data accuracy and protocol compliance.

### Statistical analysis

The statistical analyses will be performed using the SPSS for Windows, version 19.0.1, R (version 3.1.2) package for statistical analysis and STATA 13. Non-normally distributed variables will be expressed as median with interquartile range and normally distributed variables as mean ± SD, as appropriate. Between-group comparisons will be assessed for nominal variables with the Chi-square test, and by Kruskal-Wallis test or one-way ANOVA for the rest of the variables. In order to comply with the assumptions for regression analysis, logarithmic conversion will be performed for non-normally distributed variables. Pearson correlation coefficient will be used to determine correlations between variables. Stepwise multivariate regression analysis including all univariate associates (*p* < 0.05) will be used to assess the independent associations between variables. Survival and time-to-event analysis of outcomes will be performed using Kaplan-Meier cumulative survival plots and Cox proportional hazards model, including adjustment for potential confounding factors. In the multivariate Cox models, we will adjust for all variables that will be correlated to the study outcomes with *P* < 0.05 at univariate Cox analyses.

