## Methods

Data emerging from the general population suggests that COVID-19 is essentially an endothelial disease, with possible deleterious long-term effects that are currently incompletely understood. Therefore, our aim is to assess the CV risk in a CKD, dialysis and KTx population, following SARS-CoV-2 infection, by determining the long-term impact of this disease on CV and renal outcomes in the aforementioned population as compared to a control group of matched patients (see Fig. 1).

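### Controls are matched on age, sex and kidney disease, but the planned between-group tests ignore the matching, and a univariate P<0.05 screen decides whether the matching factors are adjusted for

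*Protocol article*

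**What the plan says.** Under Methods, the aim is to assess outcomes after SARS-CoV-2 infection "as compared to a control group of matched patients". Inclusion criteria define the comparators as "Age, sex and kidney disease (CKD stage 3–5, dialysis or KTx) matched patients without confirmed SARS-CoV-2 infection". The matching ratio is not given, nor is it said whether matching is by individual pair or by frequency. Study population sets the size as "divided into two groups with minimum 125 patients per group".

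Statistical analysis then plans the comparison in three parts:

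- **Between-group tests.** "Between-group comparisons will be assessed for nominal variables with the Chi-square test"; all other variables go to Kruskal-Wallis or one-way ANOVA. These are all independent-sample tests.
- **Regression.** Stepwise selection from variables that are univariate associates at p<0.05.
- **Time to event.** Kaplan-Meier plots and a Cox model that is to adjust for confounders. The following sentence makes that adjustment set the variables with P<0.05 in univariate Cox analyses.

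No paired test, matched-set stratum or clustered variance is named, and no matching factor is kept in a model by design.

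**The concern.** Matching on prognostic factors makes the two arms positively correlated. An independent-sample test ignores that covariance, so its standard error is too large: intervals are too wide and the test is conservative. The Outcome data section makes markers of CV risk and endothelial dysfunction primary alongside mortality and the CV composite, so unadjusted ANOVA or Kruskal-Wallis comparisons could carry a primary conclusion.

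The covariate rule raises a second issue. The factors that the design was built on stay in the model only if the data happen to show P<0.05. Matching balances them at baseline, but that balance is not guaranteed among patients who are still alive and attending at 6, 12 and 24 months. The sample-size section expects mortality to differ by arm, and the limitations name refusal to continue. Adjustment then protects the comparison, and the plan does not secure it.

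**Working it through.** **Inputs from the protocol article.** 125 per group; mortality 9% v 22%; alpha 0.05; power 80% (Sample size power calculation). Two-sided testing is assumed, since sidedness is not stated. The within-pair correlation ρ is not in the document, so 0 to 0.30 is an assumed range.

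**Step 1: the plan's own figure.** With independent groups, the mean risk is (0.09 + 0.22)/2 = 0.155.

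- Null SE = √(2 × 0.155 × 0.845/125) = 0.0458.
- Alternative SE = √((0.09 × 0.91 + 0.22 × 0.78)/125) = √(0.2535/125) = 0.0450.
- Power = Φ((0.13 − 1.96 × 0.0458)/0.0450) = 81.4%.

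The stated 125 is therefore consistent with an independent-groups calculation (121 per group would give 80%). Freedman's formula with HR = ln 0.78/ln 0.91 = 2.63 needs 39 events, or 39/0.31 = 126 per group.

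**Step 2: the same margins, matched in pairs.** The within-pair covariance of death is ρ × √(0.0819 × 0.1716) = 0.1185ρ.

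- Interval ratio, unpaired to paired = √(0.2535/(0.2535 − 0.2371ρ)).
- Probability that both die = 0.0198 + 0.1185ρ. This gives the total discordant proportion ψ = 0.31 − 2 × (0.0198 + 0.1185ρ).
- McNemar power = Φ((0.13√125 − 1.96√ψ)/√(ψ − 0.13²)).
- Chi-square power uses the null SE for the critical value and √((0.2535 − 0.2371ρ)/125) as the true SE.
- True type I error of the nominal 5% chi-square at equal risks = 2(1 − Φ(1.96/√(1 − ρ))).
- SE ratio for a continuous marker = 1/√(1 − ρ).

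Worked case, ρ = 0.20: interval ratio √(0.2535/0.2061) = 1.11; ψ = 0.2230; McNemar Φ((1.453 − 0.926)/0.454) = 87.8%; chi-square Φ(0.0403/0.0406) = 83.9%.

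| ρ (assumed) | Chi-square power | McNemar power | Unpaired interval too wide by | True type I error | Marker SE too large by |
|---|---|---|---|---|---|
| 0 | 81.4% | 80.6% | 0% | 5.0% | 0% |
| 0.05 | 82.0% | 82.4% | 2% | 4.4% | 3% |
| 0.10 | 82.6% | 84.2% | 5% | 3.9% | 5% |
| 0.20 | 83.9% | 87.8% | 11% | 2.8% | 12% |
| 0.30 | 85.4% | 91.2% | 18% | 1.9% | 20% |

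**Step 3: what the P<0.05 screen costs.** Two simulations were run, both with assumed covariate effects.

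*Logistic models, 2,000 runs per setting.* Where the assumed effects gave ρ of about 0.07, power was 82.1% (chi-square), 84.4% (McNemar), 84.6% (all matching factors forced in) and 84.0% (screened). At ρ of about 0.13 it was 83.8%, 88.1%, 88.2% and 88.0%.

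*Cox models.* Assumptions: age HR 1.06 per year with SD 12, dialysis HR 3 with a 40% share, sex HR 1.3. Expected deaths: 125 × 0.09 + 125 × 0.22 = 38.75, about 39.

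| Cox model | HR for COVID | Power |
|---|---|---|
| Unadjusted | 2.67 | 83.3% |
| Screened at P<0.05, as planned | 2.90 | 86.9% |
| Matching factors forced in | 2.91 | 87.3% |

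The screen costs 87.3 − 86.9 = 0.4 points and changes the HR by 0.01.

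**Step 4: what the screen drops.** In a run under the same age and dialysis assumptions, age passed in 97% of trials and dialysis in 88%. Sex at HR 1.3 passed in about 12%. The event-count approximation agrees. With a 50:50 split, z = ln 1.3 × √(38.75/4) = 0.82, so the chance of passing is about Φ(0.82 − 1.96) = 13%. The same formula gives about 24% for HR 1.5 and 58% for HR 2.0.

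**Step 5: balance after baseline.** If the stated rates are taken as 24-month mortality (the document gives no time horizon), about 125 × 0.91 = 114 controls and 125 × 0.78 = 98 COVID patients would be alive for the last marker visit, before any withdrawals. At ρ = 0 only about 125 × 0.91 × 0.78 = 89 pairs would be intact.

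**The case against.** The case for leaving the plan alone is substantial.

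- **The error is on the safe side.** A reader might infer from the mismatch that intervals are too narrow, false positives inflated or the study underpowered. None of these follows. The unpaired test has a type I error at or below 5% and at least 81.4% power in the table above. With complete follow-up, a crude comparison in a matched cohort is not confounded by the matching factors.
- **Adjusted models are already planned.** A reader might contrast the unadjusted Cox result (HR 2.67) with the fully adjusted one (HR 2.91) and conclude that the planned hazard ratio is pulled towards 1. The plan does not stop at an unadjusted Cox model, and its screened model gives 2.90. Likewise, an assumed R² of 20% to 30% for the markers could be turned into a 25% to 43% larger effective sample through 1/(1 − R²). No document gives that R², and the figure ignores the multivariate regression already planned.
- **The tests are listed generically.** No test is assigned to a named primary outcome, so chi-square and ANOVA may serve partly for description.
- **Individual pairs are not stated.** Under frequency matching, McNemar, paired tests and set-clustered errors do not apply.
- **The article is condensed**, and an analysis plan may exist.

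The first four points stand and limit the size of the concern. The last does not remove it: the article states the covariate rule outright, so an analysis plan that kept the matching factors in by design would depart from the published text.

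**Conclusion.** The concern holds as a modest matter of efficiency and robustness. The planned between-group tests ignore the matching, and the covariate rule does not secure adjustment for the matching factors.

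The loss from unpaired tests depends on a within-pair correlation that the document does not give. Over the assumed range 0.05 to 0.30, the risk-difference interval is about 2% to 18% too wide, and power is 0.4 to 5.8 points below McNemar. The loss is nil at zero correlation. These figures apply to individual pairs.

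The screen costs under one point of power and barely moves the hazard ratio when the factors are strong. Its fault is that a weaker design factor enters or leaves by chance, while baseline balance may erode through deaths and withdrawals. The simulated results rest on assumed covariate effects and complete follow-up. The document does not support a claim of bias or of inadequate power from this source.

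**What to change.** In Statistical analysis, pre-specify age, sex and kidney disease class (CKD 3–5, dialysis, KTx) in every outcome model regardless of P value. Kidney disease class can be a covariate or a Cox stratum. State that the between-arm conclusions for mortality, the CV composite and the markers rest on these adjusted models and not on the unadjusted tests.

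State whether matching is by individual pair or by frequency. If by pair, keep the matched-set identifier in the database and use set-clustered errors, or paired tests for simple comparisons. The adjusted model also retains patients whose partner is lost. If by frequency, the adjustment alone suffices.

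The cost is wording, plus one identifier column if pairs exist. The three variables are already collected, and no patient procedure changes. The statistical price is a few degrees of freedom. With kidney disease class as a covariate, the model has 5 parameters (exposure 1, age 1, sex 1, class 2), or 38.75/5 = about 8 expected deaths each. With class as a stratum it has 3, or about 13 each. Further covariates should therefore be few.
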